## Abstract

**Background:**

Depression poses a major threat to public health with an increasing prevalence in the United States. Mindfulness-based interventions, such as mindfulness-based cognitive therapy (MBCT), are effective methods for managing depression symptoms and may help fortify existing efforts to address the current disease burden. The in-person group format of MBCT, however, incurs barriers to care such as expenses, childcare needs, and transportation issues. Alternate delivery modalities such as MBCT delivered via the web can be investigated for their capacity to overcome these barriers and still reduce symptoms of depression with adequate feasibility and efficacy.

**Objective:**

This study protocol aims to examine the feasibility and efficacy of MBCT delivered via the web for the treatment of depression.

**Methods:**

To attain study aims, 2 phases will be implemented using a waitlist control design. A total of 128 eligible participants will be randomized into either an 8-week MBCT intervention group plus treatment as usual (MBCT + TAU; group 1) or an 8-week waitlist control group (group 2). In phase I (8 weeks), group 1 will complete the intervention and group 2 will proceed with TAU. In phase II (8 weeks), group 2 will complete the intervention and group 1 will continue with TAU until reaching an 8-week follow-up. TAU may consist of receiving psychotherapy, pharmacotherapy, or combined treatment. Data collection will be completed at baseline, 8 weeks (postintervention for group 1 and preintervention for group 2), and 16 weeks (follow-up for group 1, postintervention for group 2). The primary outcomes will include (1) current, residual, or chronic depression symptoms and (2) psychiatric distress. Secondary outcomes will include perceived stress and facets of mindfulness. The feasibility will be measured by assessing protocol adherence, retention, attendance, and engagement. Finally, the extent of mindfulness self-practice and executive functioning skills will be assessed as mediators of intervention outcomes.

**Results:**

This study began screening and recruitment in December 2022. Data collection from the first cohort occurred in January 2023. By November 2023, a total of 30 participants were enrolled out of 224 who received screening. Data analysis began in February 2024, with an approximate publication of results by August 2024. Institutional review board approval took place on September 11, 2019.

**Conclusions:**

This trial will contribute to examining mindfulness-based interventions, delivered via the web, for improving current, residual, or chronic depression symptoms. It will (1) address the feasibility of MBCT delivered via the web; (2) contribute evidence regarding MBCT’s efficacy in reducing depression symptoms and psychiatric distress; and (3) assess the impact of MBCT on several important secondary outcomes. Findings from this study will develop the understanding of the causal pathways between MBCT delivered via the web and depression symptoms further, elucidating the potential for future larger-scale designs.

**Trial Registration:**

ClinicalTrials.gov NCT05347719; https://www.clinicaltrials.gov/ct2/show/NCT05347719

**International Registered Report Identifier (IRRID):**

DERR1-10.2196/53966

## Introduction

Major depressive disorder (MDD) is a serious threat to health in the United States and other middle and high-income countries [1], with a lifetime prevalence rate close to 20% [2]. Those with MDD have both the symptoms of depression and impairments in quality of life [3]. Moreover, MDD can place economic burdens on families and society at large [4]. The average annual costs per depression case can range from US $1000 to $2500 for direct costs, from US $2000 to $3700 for morbidity costs, and from US $200 to $400 for mortality costs [5].

To address chronic challenges to community health such as depression, public health stakeholders seek out programs that can be easily delivered in a web-based setting [6]. Mindfulness-based interventions (MBIs) have been increasingly recognized as efficacious [7] and cost-effective [8] in addressing chronic issues in mental health and substance misuse. Originating from Eastern meditation and yoga traditions, MBIs are designed to foster greater awareness of present-moment experiences [9]. Recent evaluations found that MBIs with a standardized protocol saved health care expenditures for patients with various physical or mental health issues [10,11]. With their consistent benefit on mental health, substance misuse, and physical fitness outcomes [7,12-14], MBIs represent a promising strategy for community organizations dedicated to improving the health of their residents.

Particularly, mindfulness-based cognitive therapy (MBCT) has been shown to be an effective method of reducing symptoms of depression [15-20]. MBCT has also been shown to decrease depression symptoms in individuals with chronic and treatment-resistant depression, as well as residual symptoms of recurrent depression [21-23]. MBCT is an 8-session group intervention program designed to increase awareness of internal reactions that may lead to symptoms of depression. These internal processes may include depression-related rumination and persistent negative thoughts. By equipping individuals with techniques to detach from these dysfunctional cognitive patterns, MBCT has the potential to redirect attention to the current, present-moment experiences [20]. Additionally, MBCT has been associated with several mechanisms of change purported to impact depressive symptoms, including increases in mindfulness and self-compassion in addition to decreases in cognitive reactivity to negative, ruminative thinking [24-26].

Further, 1 challenge surrounding in-person MBCT is the financial barrier that may prevent at-risk populations from accessing the care that they need. The average cost for an 8-session program ranges from US $100 to $250 per session, making it inaccessible for individuals with limited financial resources. What is particularly striking is that individuals with lower incomes are at an increased risk for depression [27] as well as other mental health disorders [28]. This points to the importance of investigating what role MBCT delivered via the web may play for at-risk populations.

A benefit commonly associated with web-based adaptation is decreased cost [29-32]. A web-based format can reduce or eliminate expenses like facilities, food, and traveling fees [33]. Decreased costs enable the interventions to be accessible to a wider range of participants, companies, and researchers at a lower price, allowing for broader dissemination and increased study size. Technology-based delivery also addresses many issues pertinent to administering interventions, such as reaching groups who live in remote locations or who lack adequate transportation [30,34,35]. Web-based platforms enable participants to complete evidence-based intervention sessions in the privacy of their own homes, potentially protecting anonymity and reducing the stigma associated with taking part in a mental health intervention [36,37]. Finally, technology-based administration also eliminates the need to travel to sessions or arrange for childcare, increasing convenience and reducing time commitment for participants [38,39].

However, despite the numerous benefits associated with formats delivered via the web, there are challenges associated with adapting interventions originally designed for in-person delivery. Further, 1 reason for concern is that adaptations that remove fidelity, or key elements of an intervention, harm the efficacy of the intervention [40]. In addition to the potential loss of fidelity of the MBCT program, MBCT delivered via the web also presents challenges in retaining participant attention, maintaining the quality of group discussion, and combating “zoom fatigue.”

Our study will take steps to address these concerns, testing the feasibility of the web-based, or online-delivery model of MBCT. Such steps will include making recommendations to participants to keep their video on during the intervention session, remaining in a quiet area, making prior arrangements to minimize interruptions, regular check-ins during the session to stimulate participant response to exercises and questions, using headphones if available, having water and a blanket nearby in case needed, and finally, ensuring that a device charger is at hand. In addition to addressing feasibility concerns, we aim to contribute to the evidence base regarding MBCT’s efficacy in reducing depressive symptoms. Finally, we hope to add to the understanding of the causal mechanisms and factors that moderate treatment outcomes of MBCT for depressive symptoms.

## Methods

### Study Design

Our study plans to examine how MBCT delivered via the web may affect primary and secondary outcomes for individuals with a history of depression. It will also assess mediators, moderators, and the sustainability of the intervention. The following hypotheses will be assessed among program participants in the intervention group as compared to a waitlist control group, and within groups compared from pre- to postintervention.

The MBCT intervention group will show a greater reduction in depressive symptoms from TI to TII, compared to the waitlist group.The MBCT intervention group will show a greater reduction in psychiatric distress symptoms from TI to TII compared to the waitlist group.The MBCT intervention group will sustain gains through the 8-week follow-up period at TIII.The MBCT intervention will improve secondary outcomes, such as:perceived stressfacets of mindfulnessThe MBCT intervention will improve the skills associated with mechanisms of change for individuals with a history of depression, and these skills will act as mediators between MBCT and primary and secondary outcomes:extent of mindfulness self-practiceexecutive functioning skillsThe format delivered via the web will meet feasibility aims measured by adherence, retention, attendance, and engagement.

### Trial Design

Using a waitlist control design, this trial will randomize 128 eligible participants into 2 groups. In the first phase lasting 8 weeks, group 1 will partake in the MBCT intervention plus treatment as usual (MBCT + TAU) while group 2 will remain as waitlist control following TAU. In the second phase lasting 8 weeks, group 2 will begin completing the MBCT intervention, and group 1 will enter a follow-up phase, continuing with TAU. TAU will be comprised of psychotherapy, pharmacotherapy, or a combination of both. Data collection will be completed at baseline, 8 weeks (postintervention for group 1 and preintervention for group 2), and 16 weeks (follow-up for group 1 and postintervention for group 2). In this manner, our study design will ensure that both trial arms are treated fairly, and that group 1 can be followed up for 8 weeks to assess the sustainability of the intervention. Figure 1 outlines the flow of this study. The registration of this trial took place on April 22, 2022.

**Figure 1 figure1:**
[figure not shown]
Study flow. MBCT: mindfulness-based cognitive therapy; T: timepoint.

### Participants and Procedure

#### Setting

This study will be led by Prisma Healthcare System and Clemson University, in collaboration with the Prisma Health-Upstate Internal Medicine Clinic. The clinic is a branch of the Prisma Health System that provides community-based primary care and acts as an academic tertiary care site. As part of their goal to address the chronic disease burden, health care providers at the clinic screen approximately 700 patients monthly for depression.

#### Eligibility Criteria

Participants in this study must (1) be aged 18 years at a minimum, (2) speak English fluently, (3) have sixth grade and above literacy, (4) be willing to share contact information (home address, phone number, or email), (5) have no current mindfulness practice, (6) be Greenville residents or persons who are patients of the partnering organizations in our study, and (7) have current or a lifetime history of any major depressive episode. Study exclusion criteria include (1) current psychosis, dementia, moderate to severe traumatic brain injury, pregnancy, or active suicidality; (2) persistent antisocial behavior; (3) persistent self-injury requiring clinical management; (4) an acute episode of a substance use disorder episode (met 2 or more substance use disorders criteria in the past 2 weeks); (5) previously completed or currently attending an MBI; and (6) are currently younger than 18 years, are non–English speakers, or have a literacy lower than sixth grade.

#### Recruitment and Screening Procedure

Participants will be recruited from the Prisma Health-Upstate Internal Medicine Clinic who currently have or have had a lifetime history of any major depressive episode. Health care providers at the clinic will identify patients using the *ICD-11* (*International Classification of Diseases, 11th Revision*) codes [41] from the patients’ electronic medical records. Researchers will contact eligible participants and ask for verbal consent before participation in an in-person screening interview with a member of the research team. At this time, the Patient Health Questionnaire (PHQ-9) [42] is to ascertain any current depression symptoms. PHQ-9 scores of 5, 10, 15, and 20 will represent mild, moderate, moderately severe, and severe depression, respectively. If no depression symptoms are currently present, this will also be noted. Participants who meet eligibility criteria will be asked to provide written informed consent before enrolling in this study. Recruitment began in December 2022.

#### Intervention Procedures

The intervention will be delivered by 3 Licensed Clinical Social Workers who have previously undergone MBCT teacher training and become certified instructors. The intervention will consist of 8 weekly 2-hour group therapy sessions. All sessions will be delivered to a group of up to 12 participants and will take place over Zoom (Zoom Video Communications, Inc). The minimum number of participants needed to proceed with each intervention program is 7 individuals. Certified instructors will follow the standardized MBCT protocol developed by Segal et al [43] (see Textbox 1 for the outline of each session).

Mindfulness-based cognitive therapy program outline per Segal et al [43].Session 1: Awareness and automatic pilotSession 2: Living in our headsSession 3: Gathering the scattered mindSession 4: Recognizing aversionSession 5: Allowing or letting beSession 6: Thoughts are not factsSession 7: How can I best take care of myself?Session 8: Maintaining and extending new learning

MBCT integrates training in mindfulness meditation and cognitive-behavioral methods. It teaches skills designed to increase awareness of internal reactions that trigger depressive symptoms, such as depression-related rumination and negative thoughts, and provides techniques to detach from these dysfunctional cognitive processes [19]. In the first half of the program, participants will focus on learning the principal tenets of mindfulness. They will explore central themes about the tendencies of the mind to habitually engage with thoughts, which produces an array of feelings and emotions. In the latter half of the program, participants will begin the practice of becoming aware of thoughts as they arise, thereby witnessing habitual patterns that may lead to unpleasant feelings or emotions [43]. Outside of the sessions, participants will be assigned daily homework exercises and given handouts as well as audio recordings to use in their mindfulness practice. Participants who miss a session will be contacted by the research team to determine if they would benefit from medical or psychiatric assistance and to assess any barriers to upcoming sessions.

#### Study Fidelity

The intervention’s fidelity will be evaluated using the MBCT Assessment Scale [44]. Weekly session audio recordings will be archived for access by 2 members of the research team who shall conduct the assessment. They will each use the MBCT Assessment Scale to code a random selection of half of the sessions. To achieve reliability, they will conduct 10 practice assessments which will be vetted by the research team. To prevent drift, frequent recalibration meetings will be scheduled. Additionally, group facilitators will convene weekly in the presence of the licensed clinical psychologist for supervision.

#### Study Withdrawal

Participants will not be permitted to continue in this study if uncooperative behavior is displayed threatening group cohesion, or if participants undergo severe psychological or medical symptoms that warrant professional treatment. If a participant does not attend an intervention session, the research team will follow up with that individual. A record will be maintained of contact information for participants’ usual providers and other emergency contact persons, and these individuals will be contacted if the participant cannot be reached. If following 5 weekly attempts to reach a participant no response is obtained, the participant will be considered lost to follow-up. Those who wish to voluntarily discontinue participation in this study will be asked the reasoning behind their decision.

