### Sample Size

The total sample size of our trial is expected to be 128 individuals with 64 participants placed into each group. This was estimated by a 2-tailed *t* test using GPower 3.1 (Informer Technologies, Inc) software. Our calculation of sample size depended on (1) the level of significance (α error probability), which was set as .05 based on Ronald A Fisher’s suggestion [55]; (2) the expected effect size, which was set as *d*=0.5, according to Cohen classification that “a medium effect of .5 is visible to the naked eye of a careful observer” [56]; (3) the expected power of this study (1–β error probability), which was set as 0.8 based on Cohen theory [57] because we failed to obtain support from previous similar studies; and (4) the allocation ratio (N2/N1), for which we expect number of participant in treatment group and control group to be the same.

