### Statistical Methods

#### Primary Outcomes

An intent-to-treat method will be used to conduct the primary analyses. By comparing the baseline and demographic variables between groups, the randomization success will be determined. With a random intercept for a cluster of individuals, generalized linear mixed effects models (GLMMs) will be used [58] to assess the effects of MBCT on depression and psychiatric distress symptoms (hypothesis 1). Week 8 will be the primary end point for this assessment. The covariates measured at TI that are relevant but not balanced between group 1 and group 2 will be incorporated into all models. Additionally, all analysis models will include clinical site level as a fixed effect. GLMMs will be used to test the association between MBCT psychiatric distress (hypothesis 2), in addition to gains sustained at an 8-week follow-up (hypothesis 3).

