#### Secondary Outcomes, Moderators, and Mediators

GLMMs will be used to assess the association between MBCT and the secondary outcomes of perceived stress and mindfulness skills (hypothesis 4). Potential moderators of the effect of MBCT, namely treatment history, traumatic life events history, baseline depression, and their interaction with MBCT, will be looked at in their own GLMMs. Using regression coefficients, the role of moderators that these variables may play will be assessed.

Using the PROCESS macro [59] in SAS (SAS Institute), the mediators, extent of mindfulness self-practice, and executive functioning skills (hypothesis 5), will be examined via the product of the coefficient method. This will be limited to the first phase of this study lasting 8 weeks. Further, 2 separate GLMMs will be used to assess how the primary and secondary outcomes may be indirectly influenced by MBCT. By regressing the mediator and outcome, respectively, on MBCT, and controlling for the mediators as well as applicable covariates, the indirect effects of MBCT on outcomes will be examined. Parallel multiple mediator models in addition to serial multiple mediator models will be used to conduct sensitivity analysis. To examine if MBCT effects will be sustained through 8 weeks postintervention (hypothesis 3), linear mixed-effects models will be used with main effects consisting of treatment group, time, group × time interaction, and nested random effects for subjects and cluster. A regression parameter associated with group × time interaction at 0 will be the null hypothesis. This acts as an equivalent for assessing the carryover effect [60]. If rejected, there is support that the effects of the intervention remain after 8 weeks have elapsed. An imputation method will be used to address any data that are missing.

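### The withdrawal rule ends study participation, not just session attendance, on a trigger close to the primary outcomes, so the week-8 scores that intent-to-treat needs may go uncollected

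*Protocol article*

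**What the plan says.** All references are to the protocol article.

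- **Study Withdrawal** gives two grounds for removal. The first is behavioural: "Participants will not be permitted to continue in this study if uncooperative behavior is displayed threatening group cohesion". The second is clinical: "or if participants undergo severe psychological or medical symptoms that warrant professional treatment". Both end participation in the study. Neither this section nor any other says whether outcome questionnaires are still offered after removal.
- **Statistical Methods, Primary Outcomes**: "An intent-to-treat method will be used to conduct the primary analyses". Week 8 is the primary end point.
- **Primary Outcome Measures**: depression symptoms on the PHQ-9, and psychiatric distress on the depression and anxiety subscales of the Brief Symptom Inventory.
- **Secondary Outcomes, Moderators, and Mediators**: "An imputation method will be used to address any data that are missing". The method is not named.
- **Intervention Procedures** and **Trial Design**: in phase I, group 1 has eight weekly sessions, and anyone who misses one is contacted about possible medical or psychiatric need. Group 2 waits on treatment as usual.
- **Assessment Procedures**: data are collected at TI, TII (8 weeks) and TIII (16 weeks) only.
- **Dissemination**: when a distressed participant needs treatment, a clinician is contacted. Removal is not mentioned.

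**The concern.** Intent-to-treat needs the week-8 outcome from everyone randomised, including people who stopped attending or got worse. A rule that takes people out of the study because their psychological symptoms became severe does the reverse: whether a score is missing depends on how high it would have been.

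Nothing is measured between TI and TII, so worsening after baseline leaves no record in the outcome data. An imputation that draws on TI scores could recover only the part of the worsening that TI predicts.

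The arms also differ in how often the rule could be triggered. Before TII, group 1 is seen weekly and called after absences, while no study contact is described for group 2. Removal for threatening group cohesion can affect only group 1 in that period, because group 2 has no group yet. If removals for symptoms are therefore more frequent in group 1, its remaining participants look better than the arm as randomised, and the primary contrast moves toward MBCT.

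**Working it through.** **1. The plan's own figure.** Sample Size sets alpha at .05 two-tailed, d = 0.5, power 0.8 and equal allocation, giving 64 per group. The normal approximation gives n = 2(1.960 + 0.842)²/0.5² ≈ 62.8, so 63 per group. The exact noncentral t gives power 0.795 at 63 and 0.801 at 64. The stated 64 per group (128 in total) is reproduced, and the sample size is not in question. The value d = 0.5 serves below as the yardstick.

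**2. The passages side by side.**

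| Question | Group 1, weeks 0–8 | Group 2, weeks 0–8 |
|---|---|---|
| Does the symptom rule apply? | Yes | Yes |
| Scheduled study contact between TI and TII | Eight weekly sessions | None described |
| Check on psychiatric need after an absence | Yes | Cannot arise (no sessions) |
| Removal for threatening group cohesion | Possible | Cannot arise (no group) |
| Are TII scores collected after removal? | Not stated | Not stated |

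Unequal removal is thus an inference from the schedule, not something the text states.

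**3. Size of the shift.** The documents give no removal rate, so these inputs are assumptions: share removed q1 (group 1) and q2 (group 2), and correlation ρ between the severity that triggers removal and the week-8 score. The true effect is 0 and only remaining participants are analysed. Under a normal model, removing the worst share q moves an arm's mean, in SD units, by

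shift(q) = −ρ · φ(c) / (1 − q), with c = Φ⁻¹(1 − q).

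- q = 0.05: c = 1.645, φ(c) = 0.103, shift = −0.109ρ
- q = 0.10: c = 1.282, φ(c) = 0.175, shift = −0.195ρ

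The bias in the contrast is shift(q1) − shift(q2). A negative value favours MBCT. Two-sided type I error comes from simulating a two-sample t test with 64 randomised per arm, 10,000 runs per scenario.

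| Removed, group 1 / group 2 | ρ = 0.5: bias (type I error) | ρ = 0.7 | ρ = 1 |
|---|---|---|---|
| 0% / 0% | 0 (0.050) | 0 (0.051) | 0 (0.049) |
| 5% / 0% | −0.054 (0.057) | −0.076 (0.070) | −0.109 (0.094) |
| 10% / 0% | −0.097 (0.078) | −0.136 (0.119) | −0.195 (0.206) |
| 10% / 5% | −0.043 (0.058) | −0.061 (0.064) | −0.086 (0.087) |
| 10% / 10% | 0 (0.051) | 0 (0.048) | 0 (0.049) |

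**4. Against the planned effect.** One-sided removal of 5–10% produces 0.054/0.5 = 11% to 0.195/0.5 = 39% of the planned d. In people, that is 0.05 × 64 ≈ 3 to 0.10 × 64 ≈ 6 participants.

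**5. With the fix.** If week-8 scores are collected from everyone randomised, the expected bias from this source is 0, as in the 0% / 0% row, and power at 64 per group stays 0.80.

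**The case against.** The strongest reply is that one section concerns participation and the other concerns analysis, that imputation is promised, and that an article may leave both the imputation model and post-removal data collection to documents not shown. Part of this stands: the unnamed imputation method is not a fault in itself, and the article does not say that it assumes data missing at random. But the withdrawal rule is stated, not omitted, and it names the study as what the participant leaves. No analysis plan can recover a score that was never collected.

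A reader might also infer more than the text supports:

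- **That the primary contrast is biased toward MBCT.** The rule covers both arms, and no passage says that removals concentrate in group 1. The bias is conditional on unequal removal.
- **That the larger figures are the expected ones.** ρ = 1 with no waitlist removals and no imputation is close to a worst case. Removal would precede week 8 and rest on judgement, and imputation or a model using TI scores could recover some of the shift. Nor does the rule set a PHQ-9 cut-off.
- **That information on harm is lost.** Dissemination provides for contact within 24 hours of an adverse event and a team meeting on its cause. Data Monitoring Plan provides for quarterly board review. What may be lost is the later outcome score.
- **That the rule describes much of the enrolled population**, because "TAU will be comprised of psychotherapy, pharmacotherapy, or a combination of both". This drops the qualifier that symptoms be severe. Receiving treatment is not the same as developing severe symptoms, and a past episode alone suffices for eligibility.
- **That removal for disruptive behaviour favours MBCT.** It can cause one-sided missing data before TII, but no link to the PHQ-9 is stated, so its direction is unknown.

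**Conclusion.** The point holds in limited form. As worded, the rule ends study participation on a trigger closely tied to both primary outcomes, and nothing provides for outcome collection afterwards. That creates outcome-dependent missing data, which conflicts with the intent-to-treat commitment and which the unnamed imputation may not correct.

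Bias toward MBCT is plausible because phase I contact is unequal, but it is not established. Under the assumed rates it is about 0.05–0.20 SD with one-sided removal of 5–10%, 0.04–0.09 SD with 10% versus 5%, and zero with equal removal. These figures rest on a normal model, a correlation of 0.5–1 and an analysis of remaining participants. The actual size cannot be computed from the documents. The change is worth making because the loss cannot be repaired later and prevention costs little.

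**What to change.** Reconcile Study Withdrawal, both Statistical Methods subsections and Dissemination by separating the end of session attendance from the end of follow-up:

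- Whatever clinical rule ends attendance, keep inviting the participant to the TII and TIII surveys, on the web or on paper as Assessment Procedures already allows, unless consent is withdrawn.
- Record each removal and its reason by arm, so that any imbalance is visible.
- Analyse everyone as randomised, using the observed scores.

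The cost is a few extra questionnaires, a sentence in the protocol and a change of consent wording. The clinical decision about sessions is unchanged, and no view is taken on it here. Results reports 30 enrolled by November 2023, so 128 − 30 = 98 of the planned participants were still to be recruited at that date.
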